### Use of pneumococcal vaccine in the study area

In Catalonia, a region in the northeast of Spain with a population of seven million people, a publicly funded anti-pneumococcal vaccination programme for all individuals 65 years or older (with or without risk factors) and younger individuals with certain high-risk conditions (basically immunodeficiency, chronic heart or pulmonary disease, diabetes mellitus, severe liver disease or chronic nephropathy) began in October 1999. Further, it was extended for all people 60 years or older in 2002. Since then, a free PPV-23 has been offered when the patients came to the primary care services during the annual influenza vaccination campaigns or in any other visit throughout the year. Some years later, vaccination uptake reached approximately fifty percent,[31] and this provided an excellent opportunity to evaluate the vaccine's effects among the population. The potential effects of vaccination in preventing IPD and pneumonia have been analyzed in our reference population in two prior studies [32,33].

This project proposes a large population-based cohort study with the major aim of evaluating the clinical effectiveness of the PPV-23 against CAP as well as evaluating its potential role in cardiovascular prevention among the general population over 60 years.

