### Data sources

All participating PCCs have a computerized clinical record system that includes administrative data, medical conditions, prescriptions, laboratory results and registries associated with outpatient visits and diagnoses coded according to the International Classification of Diseases, 10th Revision (ICD-10). This electronic clinical record system will be used to classify vaccination status as well as to identify comorbidities or underlying conditions in cohort members and establish baseline characteristics of the cohort at study start.

During the study period, the primary care electronic registries of the nine participating PCCs will be used as a data source to identify those subjects who have suffered any study event that did not require hospitalisation and were treated as an outpatient during the 30-month study period.

Emergence and hospital diagnosis discharge databases of two reference hospitals (coded according to ICD-9-CM codes (International Classification of Diseases, 9th Revision, Clinical Modification) will be used to identify those cohort members who were admitted to hospital for any study event during the 30-month study period.

A structured data collection instrument will be used to review primary care and hospital clinical records to validate the diagnosis of all cases initially identified by ICD-10 or ICD-9 discharge codes.

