### Covariates

Covariates will be age, sex, frequency of attendance (number of outpatient visits per year), history of pneumonia in 24-month before study start, history of coronary artery disease, history of prior stroke, presence of major cardiovascular risk factors (hypertension, hypercholesterolaemia, smoking, diabetes mellitus or obesity), presence of major comorbidities (chronic heart disease, chronic pulmonary disease, severe liver disease, chronic nephropathy or cancer) and immunological status. Table 2 lists covariates and shows criteria used to measure and capture underlying conditions and comorbidities in the study cohort.

**Table 2 T2:** Definitions and criteria used to collect respiratory and cardiovascular risk factors and main comorbidities among cohort members in the CAPAMIS Study.*

UNDERLYING CONDITIONS	DEFINITIONS
**History of prior pneumonia**	Includes influenza-related pneumonia (J10.0 and J11.0), viral pneumonia (J12), pneumococcal pneumonia (J13), pneumonia due to Haemophillus influenzae (J14), bacterial pneumonia (J15), pneumonia due to other infectious organisms (J16), pneumonia in diseases classified elsewhere (J17) and pneumonia due to unspecified microorganisms (J18).

**History of coronary artery disease**	Includes angina (I20), acute myocardial infarction (I21), subsequent or recurrent myocardial infarction (I22) and chronic ischaemic heart disease (I25).

**History of stroke**	Includes haemorrhagic stroke (I60 to I62), cerebral infarction (I63) and stroke not specified as haemorrhage or infarction (I64); it does not include transient ischaemic attacks (code G45).

**Hypertension**	Defined as the presence of any code I10, I11, I12, I13 or I15.

**Hypercholesterolemia**	Defined as the presence of code E78.

**Diabetes mellitus**	Codes E10 to E14.

**Obesity**	Patients with registered code E66 (BMI>30%).

**Smoking**	Includes patients with current smoking (code F17 active at study start).

**Alcoholism**	Includes patients with code F10 active at study start.

**History of heart disease**	Includes congestive heart failure (I50), hypertensive heart disease (I11), cardiomyopathy (I42), cardiac dilatation or ventricular hypertrophy (I11.9 or I51.7) and coronary artery disease (I20, I21, I22 and I25).

**History of vascular ischaemia**	Besides coronary artery disease and stroke, it Includes atheroesclerosis (I70), acute arterial embolism or thrombosis (I74) and peripheric arterial disease or intermittent claudication (I73.9).

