### Statistical analysis

Absolute numbers, means and percentages will be computed to describe the patient population. The differences between groups will be evaluated using the chi-squared or Fisher's test for categorical variables, and the two tailed Student's test or ANOVA for continuous variables as appropriate.

The crude association between the outcomes and vaccination will be evaluated using incidence rates among vaccinated and unvaccinated subjects. The incidence of each event will be calculated as person-year considering in the denominator the sum of person-time contributed to each individual during study period.

Multivariable Cox proportional hazards models with time-varying covariates will be used to calculate hazards ratio (HR) and estimate the association between having received the pneumococcal vaccine and the time of the first outcome event during the study period. Repeated episodes will not be included in the analyses. Vaccine effectiveness will be estimated as (1 - HR) × 100.

Pneumococcal vaccination status will be a time-varying condition (e.g., individuals vaccinated after the beginning of the study) and persons will be considered to be vaccinated 14 days after vaccine administration. Annual influenza vaccine status will also be a time-varying covariate, whereas the other covariates will be defined at study start.

It will be checked for confounders, interactions and multicollinearity among the independent variables. The final models will be adjusted by all significant variables, as well as confounders and other baseline covariables judged of having clinical importance. The proportional hazards assumptions will be assessed adding the covariate by log-time interactions to the model and plotting the scaled and smoothed Schoenfeld residuals obtained from main effects model was possible [40]. Statistical significance will be set at p < 0.05 (two-tailed). The analyses will be performed using Stata/SE Version 9.1. (Stata Corp.)

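### The baseline covariates capture neither atrial fibrillation nor prior TIA, leaving vaccine effectiveness against stroke and AMI/stroke open to avoidable residual confounding of unknown size and direction

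*Protocol article*

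**What the plan says.** Main outcomes and definitions makes hospitalisation for stroke a primary endpoint and leaves TIA (ICD-9-CM 435) out of it. Rationale for sample size also gives a detectable effect for the combined AMI/stroke endpoint.

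The Covariates text lists, among others, "history of coronary artery disease, history of prior stroke, presence of major cardiovascular risk factors (hypertension, hypercholesterolaemia, smoking, diabetes mellitus or obesity". Table 2 then fixes the codes:

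- **History of stroke:** I60 to I64, with the note "it does not include transient ischaemic attacks (code G45".
- **Heart disease row:** "Includes congestive heart failure (I50), hypertensive heart disease (I11), cardiomyopathy (I42), cardiac dilatation or ventricular hypertrophy (I11.9 or I51.7", plus the coronary codes (I20 to I22, I25).
- **Vascular ischaemia row:** "Besides coronary artery disease and stroke, it Includes atheroesclerosis (I70), acute arterial embolism or thrombosis (I74", plus I73.9.

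Data sources says that the ICD-10-coded primary care record will be "used to classify vaccination status as well as to identify comorbidities or underlying conditions in cohort members". The footnote to Table 2 takes these histories from the codes registered at study start. Statistical analysis adjusts the final models for significant variables, "as well as confounders and other baseline covariables judged of having clinical importance".

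**The concern.** Atrial fibrillation and prior TIA are taken here as predictors of stroke; the documents give no risk ratios for them. If either is unequally distributed between vaccinated and unvaccinated members after adjustment, the hazard ratio for stroke absorbs the difference.

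A member with a past TIA and no other coded vascular disease is modelled as having no cerebrovascular history. A member with atrial fibrillation and none of the listed heart conditions is modelled as having no heart disease.

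The effects the study is sized to detect are small, 18% for stroke and 14% for AMI/stroke, so a shift of a few percentage points in either direction could change the conclusion.

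**Working it through.** **1. Is either condition captured anywhere in Table 2?**

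| Covariate | Codes | Atrial fibrillation? | TIA? |
|---|---|---|---|
| History of stroke | I60–I64 | no | excluded by name |
| Coronary artery disease | I20, I21, I22, I25 | no | no |
| Heart disease | I50, I11, I42, I51.7, coronary codes | no | no |
| Vascular ischaemia | coronary disease, stroke, I70, I74, I73.9 | no | no |

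The other rows (hypertension, diabetes, pulmonary disease and so on) do not contain these codes either.

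**2. The plan's own figures.** Inputs from Rationale for sample size: N = 27,000, 30 months (2.5 years), 50% coverage, two-sided 0.05, stroke 12 and AMI 8 per 1000 (taken as annual rates for the whole cohort).

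- Stroke events: 27,000 × 0.012 × 2.5 = 810. AMI/stroke events: 27,000 × 0.020 × 2.5 = 1,350.
- Schoenfeld power with equal groups: Φ(√D/2 × |ln HR| − 1.96).
- Stroke, HR 0.82: 14.23 × 0.1985 − 1.96 = 0.864, power 80.6%.
- AMI/stroke, HR 0.86: 18.37 × 0.1508 − 1.96 = 0.811, power 79.1%.

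The stated 80% is reproduced and is not in dispute.

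**3. How far could an omitted condition move the estimate?** With prevalence pV in the vaccinated, pU in the unvaccinated and risk ratio RR for stroke:

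B = [1 + pV(RR − 1)] / [1 + pU(RR − 1)], and observed HR = true HR × B.

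The documents give no prevalence by vaccination status and no RR, so every pV, pU and RR below is an assumption. The formula makes no allowance for covariates already in the model. The true HR for stroke is set to 0.82. Power is the step 2 formula at the observed HR, holding events at 810 for simplicity.

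| Assumed (vaccinated v unvaccinated) | B | Observed effectiveness | Power |
|---|---|---|---|
| TIA 3% v 2%, RR 2 | 1.03/1.02 = 1.010 | 17.2% | 77% |
| AF 10% v 8%, RR 2 | 1.10/1.08 = 1.019 | 16.5% | 73% |
| TIA 4% v 2%, RR 4 | 1.12/1.06 = 1.057 | 13.4% | 53% |
| AF 12% v 8%, RR 3 | 1.24/1.16 = 1.069 | 12.3% | 47% |
| Rows 1 and 4 together | 1.069 × 1.010 = 1.079 | 11.5% | 41% |
| AF 12% v 6%, RR 5 (strong) | 1.48/1.24 = 1.194 | 2.1% | 5% |
| Equal prevalence | 1 | 18.0% | 81% |
| AF 8% v 10%, RR 3 (reversed) | 1.16/1.20 = 0.967 | 20.7% | 91% |

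The higher power in the last row is not a gain: the estimate is too favourable. With no true effect, the same imbalance gives an apparent effectiveness of 1 − 0.967 = 3.3%.

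**4. AMI/stroke.** If the same RRs held for the composite (a further assumption), a true 14% would read as 1 − 0.86 × 1.019 = 12.4% with AF at 10% v 8% and RR 2, as 1 − 0.86 × 1.069 = 8.1% with AF at 12% v 8% and RR 3, and as 1 − 0.86 × 0.967 = 16.9% in the reversed case.

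**The case against.** A reader might infer that the stroke estimate is confounded by indication and that the vaccine will look less effective than it is, because chronic heart disease was a reason to vaccinate. The documents do not support that.

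- **Indication.** The list "basically immunodeficiency, chronic heart or pulmonary disease, diabetes mellitus, severe liver disease or chronic nephropathy" applied to people under 65. Everyone aged 65 or older was offered the vaccine from 1999 whatever their risk, and "it was extended for all people 60 years or older in 2002". TIA is not on the list. Selection is still possible: some members were under 65 during the earlier risk-based period, the vaccine was offered at primary care visits, and coverage reached only about half. But selective uptake can run either way, so the direction is open.
- **Existing adjustment.** The covariates already include age, sex, attendance, hypertension, diabetes, coronary disease, heart failure and prior stroke. These would remove part of any imbalance, so the figures above are not forecasts.
- **TIA definition.** Keeping TIA out of prior stroke mirrors the endpoint. This stands: the narrow definition is not a mistake.
- **Open model rule.** The clause on clinically important covariables leaves some room, and a fuller protocol or SAP may exist. This is only partial cover. Table 2 is an itemised list of what is collected, it defines neither condition, and it names G45 only to exclude it.
- **Prevention subsets.** A reader might also infer that the primary-prevention subset is contaminated by members with TIA. The Objectives section speaks only of subsets with certain underlying conditions and gives no rule, so their placement is unstated, not wrong.

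The gap in the code list survives these objections. A claim of demonstrated bias, or of bias in a known direction, does not.

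**Conclusion.** The point holds as a risk of avoidable residual confounding in the stroke and AMI/stroke estimates, of unknown size and direction. Neither atrial fibrillation nor prior TIA can enter the models from the covariates as defined.

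Under the assumptions shown, and with no credit for existing adjustment, a true 18% against stroke could read as roughly 12% to 17% with a moderate excess of these conditions in the vaccinated, close to zero with a strong excess, and about 21% with atrial fibrillation at 8% v 10% and RR 3. With balance there is no bias.

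The availability of G45 is explicit in Table 2. That of I48 is inferred from the record being ICD-10 coded. The sample size figures are unaffected. This is a cheap improvement to a fixed code list, not an error that invalidates the analysis.

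**What to change.** 1. Add two rows to Table 2, defined at study start from the same primary care record: atrial fibrillation/flutter (I48) and prior TIA (G45). Leave the definition of prior stroke as it is.
2. Keep both terms in the stroke and AMI/stroke models regardless of statistical significance.
3. State whether members with prior TIA count as primary or secondary prevention in the subset analyses.

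The cost is a slightly larger baseline query and two more model terms, against about 810 expected stroke events. Recording the prevalence of both conditions by vaccination status would also replace the assumptions above with data.

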### Statistical analysis

Absolute numbers, means and percentages will be computed to describe the patient population. The differences between groups will be evaluated using the chi-squared or Fisher's test for categorical variables, and the two tailed Student's test or ANOVA for continuous variables as appropriate.

The crude association between the outcomes and vaccination will be evaluated using incidence rates among vaccinated and unvaccinated subjects. The incidence of each event will be calculated as person-year considering in the denominator the sum of person-time contributed to each individual during study period.

Multivariable Cox proportional hazards models with time-varying covariates will be used to calculate hazards ratio (HR) and estimate the association between having received the pneumococcal vaccine and the time of the first outcome event during the study period. Repeated episodes will not be included in the analyses. Vaccine effectiveness will be estimated as (1 - HR) × 100.

Pneumococcal vaccination status will be a time-varying condition (e.g., individuals vaccinated after the beginning of the study) and persons will be considered to be vaccinated 14 days after vaccine administration. Annual influenza vaccine status will also be a time-varying covariate, whereas the other covariates will be defined at study start.

It will be checked for confounders, interactions and multicollinearity among the independent variables. The final models will be adjusted by all significant variables, as well as confounders and other baseline covariables judged of having clinical importance. The proportional hazards assumptions will be assessed adding the covariate by log-time interactions to the model and plotting the scaled and smoothed Schoenfeld residuals obtained from main effects model was possible [40]. Statistical significance will be set at p < 0.05 (two-tailed). The analyses will be performed using Stata/SE Version 9.1. (Stata Corp.)

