**Methods/Design:**

Cohort study including 27,000 individuals 60 years or older assigned to nine Primary Care Centers in the region of Tarragona, Spain. According to the reception of PPV-23 before the start of the study, the study population will be divided into vaccinated and nonvaccinated groups, which will be followed during a consecutive 30-month period. Primary Care and Hospitals discharge databases will initially be used to identify study events (community-acquired pneumonia, hospitalisation for acute myocardial infarction and stroke), but all cases will be further validated by checking clinical records. Multivariable Cox regression analyses estimating hazard ratios (adjusted for age, sex and comorbidities) will be used to estimate vaccine effectiveness.

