## Methods and Design

### Design, setting and study population

Population-based cohort study focused on adults over 60 years in the region of Tarragona, a mixed residential-industrial urban area in the Mediterranean coast of Catalonia, Spain.

Study subjects include 27,000 community-dwelling adults aged 60 years or more assigned to 9 participating Primary Care Centres (PCCs) in the study area, who will followed during a 30-month consecutive period. Six of the nine participating PCCs are located in Tarragona city (PCC Bonavista, PCC Torreforta, PCC Jaume I, PCC Sant Pere i Sant Pau, PCC Tarraco, PCC Sant Salvador) and three PCCs are located in nearby (less than 12 kilometres from Tarragona) smaller municipalities (PCC Salou, PCC Constanti and PCC Morell). Two reference hospitals for the study population are Hospital Joan XXIII and Hospital Santa Tecla, both located in Tarragona city (which has an overall population of approximately 120,000 all-age inhabitants).

It must be noted that, in Spain, primary care physicians are the first point of call for secondary and tertiary care and all citizens are registered in one PCC.

Inclusion criteria for the CAPAMIS cohort include: a) male or female adults aged 60 years or older as of January 1, 2009; and b) registered in any of the nine PCCs participating at study start. Exclusion criteria include residence in a long-term care facility. Subjects will be identified from primary care information systems. Figure 1 shows the study region and illustrates the location of participating centres.

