### Vaccination history

Vaccination status of cohort members will be determined by a review of the PCCs' electronic clinical records, which contain specially designated fields for pneumococcal and influenza vaccinations. We assume that information in clinical records is complete, so a subject will be considered as unvaccinated when a vaccination was not recorded in the PCC clinical record.

Pneumococcal vaccination status (including number of dose of PPV-23 received in prior 10 years) will be determined at study start and it will be reevaluated at the end of the first and second year of the study period. Similarly, influenza vaccination status will be determined at the beginning of the study (according to reception or not of a dose of flu vaccine in prior autumn) and it will also be reevaluated every year of the study period.

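### The covariates of the primary Cox models can be settled after the data are seen, and Primary Care Centre is in neither the covariate list nor the model

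*Protocol article*

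**What the plan says.** The Statistical analysis section first announces a screening step, "It will be checked for confounders, interactions and multicollinearity among the independent variables", and then gives the rule for the final models: "The final models will be adjusted by all significant variables, as well as confounders and other baseline covariables judged of having clinical importance". It adds: "Annual influenza vaccine status will also be a time-varying covariate, whereas the other covariates will be defined at study start".

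The candidate list is in the Covariates section. It begins "Covariates will be age, sex, frequency of attendance (number of outpatient visits per year), history of pneumonia in 24-month before study start" and continues with coronary disease, stroke, cardiovascular risk factors, major comorbidities and immunological status. Primary Care Centre (PCC) is not on it, and the analysis section mentions neither a centre term nor stratification by centre. Table 2 also defines alcoholism and vascular ischaemia, which the text list does not name. The abstract gives a shorter set: "hazard ratios (adjusted for age, sex and comorbidities) will be used to estimate vaccine effectiveness".

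The subjects are "assigned to 9 participating Primary Care Centres (PCCs) in the study area". On exposure, the Vaccination history section says that "a subject will be considered as unvaccinated when a vaccination was not recorded in the PCC clinical record". For events treated without admission, the Data sources section says that "the primary care electronic registries of the nine participating PCCs will be used as a data source to identify those subjects".

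**The concern.** Two separate things are at stake.

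**The adjustment set is not fixed.** Vaccination was not randomised, so the choice of covariates helps to decide the answer. The Rationale for sample size aims at effectiveness of 14% to 23%, and effects of that size can be moved by modelling choices. If covariates are admitted because they are significant, or because someone judges them to be confounders or important once the data are in hand, two analysts following the same text could reach different models. The confidence interval from the chosen model would take no account of the search.

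**Centre is left out.** The nine centres hold the vaccination record, the baseline diagnoses and part of the outpatient CAP record. If centres differ in uptake or completeness of recording, and also in recorded event rates, part of that difference will be read as vaccine effect or will mask one. Centre is known for every subject, so it can be controlled directly.

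**Working it through.** **1. The plan's own figures.** The document gives no figure for either issue. The nearest figures are the detectable effects at 80% power. With 13,500 per group, an unvaccinated risk of rate × 2.5 years, two-sided 0.05 and a comparison of two proportions, the power is 79.1% for CAP (effectiveness 20%), 81.8% for AMI (23%), 77.7% for stroke (18%) and 78.0% for AMI/stroke (14%). The stated 80% is approximately reproduced and this point does not affect it. These effects serve below as the yardstick.

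**2. Routes into the model.** The rule is a union of three:
- significant variables: criterion given (p < 0.05);
- confounders: to be checked, with no criterion given;
- covariates of clinical importance: a judgement, with no criterion given.

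No list is designated as the set that every primary model will use. The abstract, the Covariates text and Table 2 differ in what they name.

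**3. How much the undefined routes must carry.** Person-time is 27,000 × 2.5 = 67,500 years (full follow-up assumed). With the stated CAP rate taken as the unvaccinated rate, CAP events = 67,500 × 0.010 × 0.5 × (1 + 0.80) = 607.5, about 608. For a binary covariate with prevalence p and hazard ratio h, the chance of missing p < 0.05 is 1 − Φ(√(608·p(1−p))·ln h − 1.96). The values of h and p are assumed.
- h = 1.2, p = 0.30: √127.7 × 0.182 = 2.06, so 46% are missed.
- h = 1.2, p = 0.05: √28.9 × 0.182 = 0.98, so 84% are missed.
- h = 1.5, p = 0.30 and 0.05: about 0% and 41% are missed.

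These are not the chances of losing a confounder under the plan, because two other routes exist. They show how often a modest confounder would depend on those two routes alone.

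**4. Are there enough events to fix the set?** Events are rate × 67,500 with the stated rate read as the overall rate, or that × 0.5 × (1 + HR) with it read as the unvaccinated rate:
- AMI: 540 or 478;
- CAP: 675 or 608;
- stroke: 810 or 737.

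For about 20 covariates (assumed count) the smallest ratio is 478/20 = 24 events per covariate. Nine strata leave on average 478/9 = 53 AMI events each. Scarcity of events does not force selection.

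**5. Illustration of a centre effect.** Assumptions: nine equal centres, true HR = 1, uptake u rising linearly across centres, and the recorded event rate λ falling evenly on the log scale with top-to-bottom ratio R. The crude rate ratio is (Σuλ/Σu) / (Σ(1−u)λ/Σ(1−u)).

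| Uptake range | R = 1.2 | R = 1.5 | R = 2.0 |
|---|---|---|---|
| 45–55% | 0.8% | 1.7% | 2.8% |
| 40–60% | 1.5% | 3.3% | 5.6% |
| 30–70% | 3.0% | 6.5% | 10.8% |

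The entries are spurious effectiveness. If uptake and recorded rate rise together, the ratio inverts. The extreme cell then becomes 1/(1 − 0.108) = 1.12, an apparent 12% harm.

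A two-block version gives similar values. Half the centres have 40% uptake and 1.3 times the rate, and the other half have 60% uptake. The ratio is (0.4 × 1.3 + 0.6)/(0.6 × 1.3 + 0.4) = 1.12/1.18 = 0.949. With 1.5 times the rate it is 1.20/1.30 = 0.923. That is spurious effectiveness of 5% and 8%.

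These are crude ratios. Adjustment for listed covariates that vary by centre would remove some of the difference.

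**The case against.** The strongest reply is that the quoted rule keeps confounders and clinically important covariates as well as significant ones. Significance only adds variables, and the candidates are listed in advance and nearly all measured at baseline. This stands against a stronger reading that a reader might infer, namely that covariates enter by significance alone and non-significant confounders are discarded. The text does not say that. Nor does it say that the set will be chosen separately for each endpoint; it merely does not exclude it. Influenza vaccination is not left out either: it is missing from the Covariates list but is expressly in the model as a time-varying covariate.

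A second reply is that a journal article condenses a fuller protocol or analysis plan. That would answer a complaint about missing detail. Here, however, the article states a rule, and under that rule the choice follows the data.

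On centre, the objection carries weight. The article says that the centres and hospitals follow broadly similar diagnostic practice. All CAP must be confirmed by radiograph and record review. AMI and stroke are found in the databases of two shared hospitals and validated there. Frequency of attendance is a covariate. A reader might infer that centre differences will inflate effectiveness, but the document shows no such differences. The direction could also be the opposite: a centre that records more completely may show both more vaccination and more outpatient CAP, which would hide a benefit. What survives is that similar diagnosis and treatment says nothing about uptake or completeness of vaccination records, and that validation cannot recover outpatient cases that were never coded.

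**Conclusion.** The point holds in limited form. The rule leaves the adjustment set of a non-randomised primary comparison open until the data are seen, with one data-driven criterion and two undefined ones. The size of the resulting bias cannot be calculated. Confounders are lost only where the check or the judgement fails to recognise them.

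Confounding by centre is possible but not demonstrated. Its size and direction cannot be derived from the document. Under the assumed gradients it is about 1% to 11% in either direction, against detectable effects of 14% to 23%; only the steeper gradients reach a material share of those effects. It matters most for outpatient CAP, where the centres supply both exposure and part of the outcome record, and less for AMI and stroke. The power statement is unaffected. This is a cheap improvement rather than a defect that undermines the study.

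**What to change.** Replace the sentence on the final models with a rule of this kind: one adjustment set, named in advance, enters every primary Cox model regardless of significance. It consists of the covariates in the Covariates section plus time-varying influenza vaccination, and the baseline hazard is stratified by the nine PCCs.

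Before analysis, settle the nested definitions in Table 2 so that no condition enters twice. Heart disease contains coronary disease, vascular ischaemia contains coronary disease and stroke, and immunocompromise contains cancer and severe nephropathy. State also whether alcoholism and vascular ischaemia belong to the set, and bring the abstract into line. Keep data-driven models as sensitivity analyses, labelled as such.

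The cost is a change of wording. No new data are needed, since centre is known from registration. The intervals will be slightly wider if some covariates predict little.
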